
HEALTH CARE EFFICIENCY PROBLEM

It is hypothesized that the FOR technique is efficient and lowers the direct and indirect (productivity) costs in comparison with the ACDF technique. The ACDF technique is executed with instrumentation (intervertebral cage), the FOR technique does not require instrumentation and therefore medical costs are lowered when using this technique. The expectation is that the FOR technique leads to earlier and better work participation after operation, however this is an assumption. It could be that because of more neck pain after the FOR treatment, patients remain longer at home and therefore work absenteeism is higher in the FOR treatment group. An important part of this study is to investigate work resumption among CRS patients operated by one of the surgical techniques.

THE INTERVENTION TO BE INVESTIGATED

The ACDF technique is performed through the anterior cervical plane by which the pre-vertebral cervical area can be reached. A discectomy is executed and nerve root decompression will be established. An intervertebral cage is routinely placed to reach fusion on the long term.

The FOR operation is an unroofing technique. By unroofing the foramen of the cervical root, the cervical root is decompressed. The FOR operation is a simple technique with low morbidity and no additional instrumentation (cage, plate, screws) is needed.

EXISTING EVIDENCE OF EFFECTIVENESS

High Risk of bias by morphology in which one of the two techniques is preferred (soft discus compression or osteophytic compression) and surgeon's bias concerning preference for ACDF is present within the literature, concerning the comparison of FOR against ACDF in patients with cervical radiculopathy. No randomized clinical trial (RCT) has been performed comparing both techniques concerning relief of arm pain, cost-effectiveness and work absenteeism.

INNOVATIVE CHARACTER

The innovative value of this trial is threefold:

1) There is insufficient high quality knowledge available which technique has the best outcome for a specific subgroup of patients with a CRS due to a lateral or foraminal compression. No randomized controlled trial has been executed within this group of patients.

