The presented studies of clinical effectiveness demonstrate a similar effect on relief of arm pain, but a lower chance of serious complications needing longer hospital stay or readmission. We assume a 10% difference between the ACDF and FOR, which means that serious complications would occur in 10% more of the cases in the ACDF, and 2 weeks extra hospital care attributed to a serious complication (10 work days). We also assume that of the 1300 patients treated per year, 50% will be among the working population, in a 75% part-time job on average. The standard mean costs of a working day in the Netherlands is €230 (11). Thus: 650 working patients x 10% with serious complications x 7.5 workdays lost per patient = 487.5 work days saved with the FOR procedure. This amounts to a total of €112.125.

1. **OBJECTIVES**

Primary Objective:

Is the posterior cervical foraminotomy (FOR) technique effective in comparison to the anterior cervical discectomy with fusion (ACDF) with regards to reduction of cervical radicular pain measured by the ODOM criteria (4 point Likert scale) and VAS arm pain.

Secondary Objective(s):

- 1. Does the FOR operation lead to faster return to work, after operation, in comparison with the ACDF technique,
  2. Does the FOR operation lead to a higher quality of life in comparison with the ACDF technique,
  3. Does the FOR operation lead to more or less neck disability and/or more or less postoperative neck pain in comparison with the ACDF technique,
  4. Does the FOR operation lead to less or more complications in comparison with the ACDF technique,
  5. Does the FOR operation lead to lower productivity losses and medical costs in comparison with the ACDF technique.
  6. What would be the budget impact of implementing the FOR technique, if it were to replace the ACDF technique as the recommended strategy for patients with a CRS due to soft disc compression or osteophyte compression of a cervical root

1. **STUDY DESIGN**

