  - Report and record (S)AE
- Visit 3.1: 1 week after discharge; arm and neck pain VAS (web based)
- Visit 3.2: 2 weeks after discharge; arm and neck pain VAS (web based)
- Visit 3.3: 3 weeks after discharge: arm and neck pain VAS (web based)
- Visit 3.4: 4 weeks after discharge: arm and neck pain VAS (web based)
- Visit 3.5: 5 weeks after discharge: arm and neck pain VAS (web based)
- Visit 4: 6 weeks after operation (± 1 week) (at outpatient clinic)
  - Clinical evaluation (signs, symptoms, strength, reflexes)
  - Odom’s criteria
  - Web based patient self-assessment on pain, quality of life and costs (questionnaires: arm pain VAS, neck pain VAS, WAI, EQ-5D, NDI, iPCQ, iMCQ)
  - Report and record (S)AE
  - Costs
- Visit 5: 26 weeks after operation (± 2 weeks) (patients do not attend the hospital)
  - Web based patient self-assessment on pain, quality of life and costs (questionnaires: arm pain VAS, neck pain VAS, WAI, EQ-5D, NDI, iPCQ, iMCQ)
  - Odom’s criteria
  - Report and record (S)AE
  - Costs
- Visit 6: 52 weeks after operation (± 4 weeks) (patients do not attend the hospital)
  - Web based patient self-assessment on pain, quality of life and costs (questionnaires: arm pain VAS, neck pain VAS, WAI, EQ-5D, NDI, iPCQ, iMCQ)
  - Odom’s criteria
  - Report and record (S)AE
  - Costs
- Visit 7: 78 weeks after operation (± 4 weeks) (patients do not attend the hospital)
  - Web based patient self-assessment on pain, quality of life and costs (questionnaires: arm pain VAS, neck pain VAS, WAI, EQ-5D, NDI, iPCQ, iMCQ)
  - Odom’s criteria
  - Report and record (S)AE
  - Costs
- Visit 8: 104 weeks after operation (± 4 weeks) (patients do not attend the hospital)
  - Web based patient self-assessment on pain, quality of life and costs (questionnaires: arm pain VAS, neck pain VAS, WAI, EQ-5D, NDI, iPCQ, iMCQ)
  - Odom’s criteria
  - Report and record (S)AE
  - Costs

1. **STUDY POPULATION**
   1. **Population (base)**

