**5.1 Investigational treatment**

ACDF technique:

Microsurgical discectomy is performed through a ventral approach described by Smith and Robinson (1958). Procedure can be executed with microscope or loupe magnification. Exploration of the intervertebral disc and removal of bony spurs with a high-speed drill. Removal of the posterior part of the intervertebral space. The posterior ligament is dissected and removed with rongeurs. Subligamentous discal fragments are removed. The proximal part of the neuroforamen is inspected for discal remnants. If an osteophytic component is present, the uncovertebral joint is reduced to remove the osteophytic component. An intervertebral spacer is placed to keep height of the intervertebral disc space. No additional plate fixation is used.

FOR technique:

All patients are operated in prone position with the head fixated in a 3-point head holder. After determining the correct level on lateral radiograph, a vertical 4 cm midline incision is made, and the lateral lamina/medial facet joints are exposed. A retractor is placed adequately. Under the operating microscope or loupe magnification and after a second confirmation of the correct level, a partial hemi-laminectomy and foraminotomy with partial factectomy of the involved level is performed with high-speed drills. The percentage of the facet resection is based on the extent of the foraminal pathology. In cases of pure soft discs, the proximal root is visualized adequately for removal of the compressing disc material. In cases of foraminal stenosis, bony decompression and skeletonization of the proximal root are performed carefully using a 4-mm diamond burr, small rongeurs, and dissectors.

1. **METHODS**
   1. **Study parameters/endpoints**
      1. **Main study parameter/endpoint**

The main study parameter is to compare the clinical outcome (decrease in radiculopathy assessed by (Visual Analogue Scale for self-reported brachialgia /Odom’s criteria) between patients operated with the FOR technique or with the ACDF technique during 24 months of follow up.

Secondary study parameters are:

1. Changes in work ability (Work Ability Index, single item) during 24 months of follow up between the two groups.
2. Changes in quality of life (EQ-5D) during 24 months of follow up between the two groups.
3. Changes in neck pain (VAS during 24 months of follow up between the two groups .
4. Changes in Neck Disability Index (NDI) during 24 months of follow up between the two groups .

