5. Number or percentage of complications in the short (30 days) and long term period (104 weeks) between the two groups
6. Cost-effectiveness (104 weeks)
7. Budget impact (extrapolated to 5 years)
   1. **Randomisation, blinding and treatment allocation**

Enrolment will be performed in the 6 Centres in the Netherlands. Patients are randomized to either FOR or ACDF. Randomization will be executed per patient per Centre by web based block randomization after the informed consent procedure is fulfilled. The Trial Coordination Centre will facilitate the randomization. Number of inclusions per Centre is described in the patient enrolment plan as described in section 6.3 (study procedures).

- 1. **Study procedures**

If the patient seems to be eligible for a surgical procedure, the patient will be invited for a consultation with the neurosurgeon. He/she will inform the patient about the surgical procedure and the possibility to participate in the FACET study. The neurosurgeon will provide the patient with the study-information.

After one week, the patient can let the neurosurgeon know if he/she wants to participate in the study. Subjects who fulfil the inclusion and exclusion criteria and signed the informed consent will proceed to have the surgical procedure. Before the procedure patients will be clinically evaluated by the surgeon and anesthesiologist to be sure the surgical procedure can be performed. Which procedure is decided by randomization. Randomization will take place before the surgical procedure will be performed and after informed consent is signed. The surgeon and the patient will know to which procedure the patient is randomized. The patient will be admitted to the hospital before the procedure and will be monitored by standard hospital practice before and after the procedure. The patient will be discharged from the hospital if he/she is stable according to the responsible physician. Normally a hospital admission for this procedure takes 2-3 days. The patient will be reviewed at the outpatient clinic at 6 weeks after the surgical procedure, which is standard care. At baseline, 6, 26, 52, 78 and 104 weeks after the surgical procedure the patient is invited to fill out a web based self-administered questionnaire to monitor work ability, arm and neck pain, quality of life, complications and costs according to the visit plan (table 1).

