**Table 1. Time points and calculations for iMCQ and iPCQ**

| **Time points** | **Questionnaire** | **Recall period** | **Multiplication** |
| --- | --- | --- | --- |
| 6 weeks after surgery | iMCQ | 6 weeks | none |
|  | iPCQ | 6 weeks | none |
| 6 months after surgery | iMCQ | 3 months | x 1.5 |
|  | iPCQ | 4 weeks | x 5 |
| 12 months after surgery | iMCQ | 3 months | x 2 |
|  | iPCQ | 4 weeks | x 6.5 |
| 18 months after surgery | iMCQ | 3 months | x 2 |
|  | iPCQ | 4 weeks | x 6.5 |
| 24 months after surgery | iMCQ | 3 months | x 2 |
|  | iPCQ | 4 weeks | x 6.5 |

*Abbreviations:* the Institute for Medical Technology Assessment Medical Consumption Questionnaire (iMCQ), the Institute for Medical Technology Assessment Productivity Cost Questionnaire (iPCQ)

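### Secondary Objective 1 (faster return to work) has no matching endpoint, return date or analysis, and the costing rule scores a return between weeks 6 and 22 as zero absence

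*Combined protocol and SAP*

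**What the plan says.** Section 2, Secondary Objective 1, asks: "Does the FOR operation lead to faster return to work, after operation, in comparison with the ACDF technique". The Introduction (health care efficiency problem) gives the question weight: "An important part of this study is to investigate work resumption among CRS patients operated by one of the surgical techniques".

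The secondary parameters in section 6.1 contain one work item: "Changes in work ability (Work Ability Index, single item) during 24 months of follow up between the two groups". The Summary also lists productivity costs by iPCQ as a secondary outcome, and section 6.3 describes the iPCQ under costs. Section 3 and Table 1 of the protocol place the full questionnaires at baseline and at weeks 6, 26, 52, 78 and 104. The weekly web contacts in between, up to week 5, collect arm and neck pain only.

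The protocol text gives no recall period. Supplementary Table 1 does. At 6 weeks the row reads "iPCQ | 6 weeks | none", and at 6 months "iPCQ | 4 weeks | x 5". Later visits also use a 4-week recall, multiplied by 6.5.

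Section 8.2 plans Kaplan-Meier and Cox methods for critical events that it does not define; return to work is not named. The Introduction (anticipated cost-effectiveness) says that Dutch hospital records do not hold work-resumption data, so they cannot fill the gap.

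**The concern.** The objective is about speed, and nothing in the listed parameters measures speed. The Work Ability Index item rates perceived ability to work; it does not record when a patient went back. The iPCQ can show absence, but between weeks 6 and 22 it has no recall window.

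Two things are at stake. First, the return-to-work comparison is left to be defined after the data are seen, with return times in weeks 6 to 22 unlocated. Second, the factor of 5 carries the absence level of weeks 22 to 26 back over the previous 16 weeks. If absence falls with time since surgery, the last four weeks are the lowest part of the interval, so absence is understated. A difference between arms that arises and closes within weeks 6 to 22 disappears from the absenteeism cost. That cost feeds Secondary Objective 5 and the societal cost-effectiveness analysis.

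**Working it through.** **Reproducing the factors.** Interval length divided by recall: (26 − 6)/4 = 5, and (52 − 26)/4 = 6.5. Both agree with Supplementary Table 1.

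**Coverage.** Weeks 0 to 6 are fully recalled. Weeks 6 to 26: 4 of 20 weeks seen (20%), 16 unseen. Weeks 6 to 104: 4 × 4 = 16 of 98 weeks seen, 82 unseen (84%).

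**How one return is scored.** Take a patient absent continuously from surgery who returns at week t. True absence in weeks 6 to 26 is t − 6. The rule scores 0 if t is at most 22, and 5 × (t − 22) if t is between 22 and 26.

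| Return at week | True absence after week 6 (weeks) | Scored (weeks) |
|---|---|---|
| 8 | 2 | 0 |
| 12 | 6 | 0 |
| 22 | 16 | 0 |
| 24 | 18 | 5 × 2 = 10 |
| 26 | 20 | 5 × 4 = 20 |

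For a single return in this interval the two agree only at week 26.

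**In euros.** The Introduction prices a working day at EUR 230 and assumes 75% part-time work. An assumed return at week 12 omits 6 × 5 × 230 = EUR 6,900, or 0.75 × 6,900 = EUR 5,175, for that one patient. As an illustration between arms, suppose one arm returns at week 8 and the other at week 12. Both score zero, and a difference of 4 × 5 × 230 = EUR 4,600 per worker (EUR 3,450 at 75%) is hidden. These return times are assumptions.

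**Friction limit.** The notes to Supplementary Table 3 stop counting loss after 85 days of complete absence. Week 12 is day 84, so the EUR 6,900 stands if the count starts at surgery. On that basis the most that can be omitted after week 6 is (85 − 42)/7 × 5 × 230 = about EUR 7,060 with calendar days, or (85 − 30) × 230 = EUR 12,650 with working days. If leave before surgery counts, the omission may be nil for some patients: Supplementary Table 2 shows 22 of 45 and 20 of 55 sick-listed patients already beyond 85 days at baseline.

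**Precision for the objective.** The documents give no return curve, so I assumed exponential and Weibull curves with medians of 4 to 16 weeks. Each interval that starts with a proportion S still absent, and has conditional return probability h, contributes 0.25 × S × (1 − h) × [ln(1 − h)]² / h to the information on the log hazard ratio. I compared the sum over the plan's recall windows and gaps with the sum over daily intervals.

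| Assumed curve | Returns falling in weeks 6–26 | Information kept |
|---|---|---|
| Exponential | 34–49.5% | 84–96% |
| Weibull, shape 1.5 | 28–67% | 64–89% |
| Weibull, shape 2 | 21–80% | 45–81% |

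This takes daily resolution inside each recall window. If the forms give only absent or not absent, the lower ends become 79%, 62% and 45%.

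**Power, as an illustration.** With d returns, power = Φ(√(d/4) × ln HR − 1.96). Supplementary Table 2 implies 45/0.56 ≈ 80 and 55/0.61 ≈ 90 patients, about 170 in all. Assume that all of them return and that HR = 1.5. Power is then 75% with exact dates, 66% at 80% information and 46% at 50%. With 100 returns the figures are 53%, 44% and 30%.

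**The case against.** The strongest reply is that the data still speak to the question. Weeks 0 to 6 are fully recalled, so an early difference is seen in both absence and cost. Arms can be compared on return by week 6 and on absence in weeks 22 to 26, and a return in between is interval-censored. This stands. A reader might infer that the objective cannot be answered; the information figures above show lost precision instead. A reader might also infer that most returns fall in weeks 6 to 26. No figure in the documents supports that, and the assumed curves give anything from 21% to 80%.

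The absence of a return date is inferred from silence. The iPCQ items are not reproduced, and the baseline table reports sick-leave spells beyond 85 days, so longer durations were obtained at least once. That would help for patients still absent at a visit. It would not date a return in weeks 6 to 22 for someone already back by week 22.

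The iPCQ is itself a listed secondary outcome, and section 3 names absenteeism among the secondary measurements, so the Work Ability Index is not the only work measure. Secondary endpoints are exploratory (section 8.2). Both points lower the weight of the issue, but neither supplies an endpoint or an analysis for return to work.

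Two euro readings should be resisted. Pricing all 16 unseen weeks (16 × 5 × 230 = EUR 18,400) ignores the friction limit. Setting a one-patient omission against the plan's EUR 2,961 procedure saving is not like for like, because the latter is a mean difference between arms, while the omission can occur in both arms and only among workers.

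**Conclusion.** The point holds with moderate confidence. Secondary Objective 1 has no defined endpoint, listed date or named analysis. On the stated recall periods, returns in weeks 6 to 22 are known only to within 16 weeks and score zero absence for weeks 6 to 26. The loss of precision depends on an unknown return curve. The omitted cost is EUR 6,900 for one full-time patient returning at week 12, if the 85-day count starts at surgery.

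No bias between arms has been estimated, because the documents hold no follow-up return times. In particular, a reader might take the EUR −110 difference in paid absenteeism in Supplementary Table 3 as a product of the scaling rule. The documents neither show nor exclude that. The primary endpoint is not affected.

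**What to change.** Add to the 6, 26 and 52-week web questionnaires the date of first partial return and the date of full return to paid work. Define the endpoint as time from surgery to return among patients in paid work before surgery. Analyse it with the Kaplan-Meier and Cox methods already in section 8.2, stratified by centre because randomisation is by centre. Use the dates, under the friction rule, for absence cost in weeks 6 to 26 in place of the factor 5, and state whether the 85 days run from surgery or from the start of the sick-leave spell.

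The supplement already reports results, so new items may come too late for this trial. Where dates are missing or data are already collected, use an interval-censored analysis. Add a sensitivity analysis that interpolates between the 6-week and 26-week absence rates, and state the limitation when reporting Objectives 1 and 5.

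The cost is one or two extra items, slightly more patient burden and a small change to the cost calculation. The fallback needs no new data.

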**5.1 Investigational treatment**

ACDF technique:

Microsurgical discectomy is performed through a ventral approach described by Smith and Robinson (1958). Procedure can be executed with microscope or loupe magnification. Exploration of the intervertebral disc and removal of bony spurs with a high-speed drill. Removal of the posterior part of the intervertebral space. The posterior ligament is dissected and removed with rongeurs. Subligamentous discal fragments are removed. The proximal part of the neuroforamen is inspected for discal remnants. If an osteophytic component is present, the uncovertebral joint is reduced to remove the osteophytic component. An intervertebral spacer is placed to keep height of the intervertebral disc space. No additional plate fixation is used.

FOR technique:

All patients are operated in prone position with the head fixated in a 3-point head holder. After determining the correct level on lateral radiograph, a vertical 4 cm midline incision is made, and the lateral lamina/medial facet joints are exposed. A retractor is placed adequately. Under the operating microscope or loupe magnification and after a second confirmation of the correct level, a partial hemi-laminectomy and foraminotomy with partial factectomy of the involved level is performed with high-speed drills. The percentage of the facet resection is based on the extent of the foraminal pathology. In cases of pure soft discs, the proximal root is visualized adequately for removal of the compressing disc material. In cases of foraminal stenosis, bony decompression and skeletonization of the proximal root are performed carefully using a 4-mm diamond burr, small rongeurs, and dissectors.

1. **METHODS**
   1. **Study parameters/endpoints**
      1. **Main study parameter/endpoint**

The main study parameter is to compare the clinical outcome (decrease in radiculopathy assessed by (Visual Analogue Scale for self-reported brachialgia /Odom’s criteria) between patients operated with the FOR technique or with the ACDF technique during 24 months of follow up.

Secondary study parameters are:

1. Changes in work ability (Work Ability Index, single item) during 24 months of follow up between the two groups.
2. Changes in quality of life (EQ-5D) during 24 months of follow up between the two groups.
3. Changes in neck pain (VAS during 24 months of follow up between the two groups .
4. Changes in Neck Disability Index (NDI) during 24 months of follow up between the two groups .
5. Number or percentage of complications in the short (30 days) and long term period (104 weeks) between the two groups
6. Cost-effectiveness (104 weeks)
7. Budget impact (extrapolated to 5 years)
   1. **Randomisation, blinding and treatment allocation**

Enrolment will be performed in the 6 Centres in the Netherlands. Patients are randomized to either FOR or ACDF. Randomization will be executed per patient per Centre by web based block randomization after the informed consent procedure is fulfilled. The Trial Coordination Centre will facilitate the randomization. Number of inclusions per Centre is described in the patient enrolment plan as described in section 6.3 (study procedures).

- 1. **Study procedures**

If the patient seems to be eligible for a surgical procedure, the patient will be invited for a consultation with the neurosurgeon. He/she will inform the patient about the surgical procedure and the possibility to participate in the FACET study. The neurosurgeon will provide the patient with the study-information.

After one week, the patient can let the neurosurgeon know if he/she wants to participate in the study. Subjects who fulfil the inclusion and exclusion criteria and signed the informed consent will proceed to have the surgical procedure. Before the procedure patients will be clinically evaluated by the surgeon and anesthesiologist to be sure the surgical procedure can be performed. Which procedure is decided by randomization. Randomization will take place before the surgical procedure will be performed and after informed consent is signed. The surgeon and the patient will know to which procedure the patient is randomized. The patient will be admitted to the hospital before the procedure and will be monitored by standard hospital practice before and after the procedure. The patient will be discharged from the hospital if he/she is stable according to the responsible physician. Normally a hospital admission for this procedure takes 2-3 days. The patient will be reviewed at the outpatient clinic at 6 weeks after the surgical procedure, which is standard care. At baseline, 6, 26, 52, 78 and 104 weeks after the surgical procedure the patient is invited to fill out a web based self-administered questionnaire to monitor work ability, arm and neck pain, quality of life, complications and costs according to the visit plan (table 1).

